### Statistical Methods and Analysis

#### Sample Size

The sample size is estimated using the sample size formula for estimating proportion between two groups**.** Considering the reported fall incidence with FRIDs as 73% [12], the sample size is estimated to be 478 (each arm: 239), with 90% power (as the outcomes measures are only falls and do not include any mortality, we have set the power to 90%) and 5% level of significance to detect a minimum of 20% reduction in falls in the intervention group relative to the control group (relative risk reduction of 20%). Considering the dropout of 10%, the final sample size will be 526 (263 in each arm). A total of135 participants are expected to be recruited from each center.

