#### Data Analysis

The data will be entered in Research Electronic Data Capture (REDCap) and will be analyzed using Stata (version 16; StataCorp) software. Data will be stored in a secure server or cloud-based platform. A principal investigator and a co–principal investigator will have access to the REDcap data. The statistician will be given access to the blinded REDcap data. The occurrence of falls and fall risk during the study period will be summarized as frequency and percentages. The number of falls at these time points will be reported using the median (IQR) values. The fall risk score will be reported as mean (SD) or median (IQR) based on the normality of the data. The Mann-Whitney *U* test and Friedman test (chi-square test) will be used to analyze the change in the frequency of falls (%) at each time point between the groups and within the groups, respectively. The chi-square test will be used to analyze the fall risk score category at each time point between the groups. Additionally, repeated measures ANOVA (or Friedman test) and unpaired *t* test (or Mann-Whitney *U* test) will be used to assess the within-group fall risk score at different time points and at each time point within the group, respectively. Poisson regression analysis (both bivariate and multivariate) will be conducted to explore the association between the dependent variable (ie, the number of falls and fall risks assessed using Timed Up and Go and the Performance-Oriented Mobility Assessment) and independent factors (eg, age, gender, education, chronic illness, and intervention category). Adjusted risk ratios with 95% CIs will be reported for the factors included in the multivariate Poisson regression model. The rationality of prescriptions will be summarized using frequencies and percentages. Subgroup analysis will be performed for participants with recurrent fall history and different age categories.

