#### Incremental Cost-Effectiveness Ratio (ICER)

Incremental Cost-Effectiveness Ratio (ICER) will be calculated by dividing the difference in costs between the interventions by the difference in outcomes. The ICER represents the additional cost per unit of outcome achieved by one intervention compared to another.

We will be following the intention-to-treat strategy to analyze the data. Therefore, even participants who discontinue but have at least 1 follow-up will be included in the study to achieve the required sample size, taking into account their age and health status.

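### The plan counts early discontinuers as included under intention-to-treat, but the Friedman and visit-by-visit tests it names leave them out of the later results

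*Protocol article*

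**What the plan says.** The rule on who is analysed stands in the Protocol article at the end of the section on the Incremental Cost-Effectiveness Ratio. Its wording is general and not confined to the cost analysis: "We will be following the intention-to-treat strategy to analyze the data". The next sentence says that "even participants who discontinue but have at least 1 follow-up will be included in the study to achieve the required sample size".

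The tests stand in the Data Analysis section:

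- **Falls.** Mann-Whitney and Friedman tests "will be used to analyze the change in the frequency of falls (%) at each time point between the groups and within the groups, respectively". Mann-Whitney is thus the between-arm test at each time point and Friedman the within-group test over time.
- **Fall-risk category.** "The chi-square test will be used to analyze the fall risk score category at each time point between the groups".
- **Fall-risk score.** The choice for change over time is "repeated measures ANOVA (or Friedman test". With the tests at each visit, the sentence runs "repeated measures ANOVA (or Friedman test) and unpaired *t* test (or Mann-Whitney *U* test) will be used to assess the within-group fall risk score", over time and at each time point. The sentence literally places the unpaired test within the group. An unpaired test compares independent groups, so it is read here as the between-arm comparison at each visit. That wording is a separate matter.
- **Poisson regression** for number of falls and for fall risk, with intervention category among the factors, described as exploring associations.

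The Follow-Up Phase section schedules visits every 3 months for a year, plus monthly calls and a diary. The Sample Size section allows for 10% dropout and arrives at 263 per arm.

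**The concern.** The two statements do not fit together. A participant last seen at month 3 is included by the stated rule, yet forms no complete Friedman block and is absent from every comparison at months 6, 9 and 12. The plan also counts on such participants to reach the required sample size.

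What is at stake is who is analysed and what the result is called. Change in fall-risk scores is a stated efficacy measure (Abstract, Results). A month-12 comparison of attenders reported as intention-to-treat would claim a protection it lacks. Participants and the intervention team are unblinded, so the reasons for leaving could differ by arm. If patients who are getting worse leave one arm more than the other, the attenders' difference is biased, in either direction.

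**Working it through.** **1. The plan's own figures.** The control proportion is 0.73, and a 20% relative reduction gives 0.73 × 0.8 = 0.584. At 5% two-sided (sidedness is not stated, so two-sided is assumed) and 90% power, the continuity-corrected two-proportion formula gives 234 per arm against the stated 239, a gap of 5/239 = 2.1%. For dropout, 239 × 1.10 = 262.9, so 263 per arm and 526 in total, as stated.

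**2. What each named method uses from a participant who leaves after the first follow-up.**

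| Method | Role in the plan | What is used |
|---|---|---|
| Friedman | within group, over time | nothing: one missing time point removes the participant |
| Mann-Whitney, t, chi-square | at each time point | only time points with data |
| Repeated measures ANOVA, complete-case form | within group | nothing |
| Repeated measures ANOVA, long format | within group | the visits observed before leaving |
| Poisson regression | association with number of falls and fall risk | can include the participant |

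**3. Size of the Friedman loss.** At 10% dropout, 263 × 0.90 = 236.7, so about 237 complete blocks and about 26 lost per arm (52 in total). In one simulated arm of 263 in which every dropout had at least one follow-up, all 263 met the inclusion rule and 237 formed complete blocks. The Friedman statistic could not be computed with the gaps left in. A long-format ANOVA kept all 263 participants and 1264 of 263 × 5 = 1315 rows.

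If the remaining participants also miss single visits at random with probability m (assumption: 2% to 5%), the share dropped over four quarterly visits is 1 − 0.90 × (1 − m)^4:

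- m = 2%: 1 − 0.90 × 0.9224 = 17.0%, about 45 of 263 per arm.
- m = 5%: 1 − 0.90 × 0.8145 = 26.7%, about 70 of 263 per arm.

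**4. Numbers available at each visit.** With dropout at a constant rate over the year (assumption), 263 × 0.90^(month/12) gives 256, 250, 243 and 237 per arm at months 3, 6, 9 and 12. On this pattern 263 − 256 = 7 of the 26 leave before the first quarterly visit. The rule would then cover 256 − 237 = 19 to 26 of them, depending on when they leave and whether a phone call counts as a follow-up.

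**5. Possible bias at month 12.** Nothing in the documents fixes this, so it was simulated: 239 per arm, five visits, correlation 0.6 + 0.4 × 0.5^lag, true benefit 0.25 SD, about 10% loss. All of these except the 239 and the 10% are assumptions.

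- Loss tied to a poor last score equally in both arms: 0.245 among attenders, a bias of 0.005/0.25 = 2%.
- Loss tied to the score in the control arm only: 0.197 among attenders, (0.25 − 0.197)/0.25 = 21% too small. A likelihood model on all visits gives 0.257.
- A second simulation with stronger dependence (log-odds 1.5 per SD): 0.149 among attenders with the control-arm mechanism, against 0.246 using all observed visits and baseline. With the same mechanism in both arms it gave 0.227 at about 8% loss.

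Dropout in these runs depends on observed scores, the condition under which the likelihood model is valid. They therefore show that model at its best.

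**6. Power.** With 237 per arm, the two-proportion comparison of 0.73 and 0.584 has about 92% power (normal approximation, no continuity correction).

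**The case against.** The strongest defence is that the article is condensed and that imputation, if planned elsewhere, would let the same tests use everyone. The absence of a missing-data method is indeed no finding here. What remains is that both the inclusion rule and the tests are stated, and as stated the tests do not honour the rule.

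A second defence is that discontinuing may mean stopping the intervention while still attending. Such participants would have all their visits and no conflict would arise. The condition of at least one follow-up, and the tie to the required sample size, point to lost visits instead, but the text does not settle it.

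Other objections stand and limit the point:

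- A reader might infer that every analysis over time becomes a completers' analysis. It does not. A long-format ANOVA keeps earlier visits, discontinuers count at each visit they attended, and the Poisson regression can include them.
- A reader might infer that the Friedman loss biases the comparison of arms. As planned, Friedman is a within-group test and yields no between-arm estimate. Any such bias comes only from the visit-wise tests.
- A Friedman test of falls over 12 monthly calls would drop 29% to 51% by the same formula with 12 in place of 4. The plan does not say its time points are monthly, and the diary and quarterly visits can recover falls from a missed call. That figure should not be relied on.
- The trial is sized on the proportion falling, and the simulations concern scores only. No bias in a falls comparison has been shown.

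**Conclusion.** The point holds for the within-group Friedman test and for the visit-by-visit tests, and no further. At the plan's own dropout the Friedman test loses about 26 of 263 per arm, rising to about 45 to 70 if 2% to 5% of single visits are also missed (assumption). Between-arm results at later visits, including month 12, are attenders' comparisons.

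Whether those comparisons are biased cannot be known from the documents. The bias is small when dropout behaves alike in both arms. It was 21% in one simulation and (0.25 − 0.149)/0.25 = 40% in another when score-related loss was placed in the control arm alone, a mechanism that is assumed and that nothing in the plan predicts.

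It might also be inferred that the trial falls short of its sample size. It does not: 237 per arm is close to the planned 239. The fault lies in the selection of patients and in the intention-to-treat label. It is worth correcting before analysis.

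**What to change.** - **TUG and POMA scores.** Make the between-arm analysis one mixed model per score, fitted to all observed visits of every participant with any follow-up, with arm, visit, arm-by-visit and baseline score. Report the month-12 arm difference with its confidence interval.
- **Falls over time.** Use a repeated-count model on all observed periods.
- **Tests that are kept.** Label Friedman and visit-wise results as complete-case or attender descriptions, not intention-to-treat, and give the number analysed for each.
- **Wording.** State whether discontinuing means stopping the intervention or leaving follow-up.

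The cost is a rewording of the analysis section and standard commands in Stata, which the plan already names. No new data are needed. The downside is that these models assume missingness depends on observed data, and TUG may need a log scale.

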#### Baseline Assessment

Demographic details, such as age, gender, occupation, education, BMI, disease conditions details, and list of drugs used (including FRIDs with their costs and orthostatic hypotension details) will be collected from all the participants. Drug details, such as the name of the drug, indication, frequency, route of administration, and duration of use will also be collected. The rationality of the prescriptions will be assessed by the World health Organization prescription indicators.

Participants will then be asked about their previous fall history using the fall history questionnaire of McCrum 2020 [8] and their concern for falls assessed by the Fall Efficacy Scale [9,10]. Quality of life will be assessed by administering the EQ-5D-5 L questionnaire. Once the baseline data collection is completed, they will be assessed for fall risk. The fall risk assessment will be conducted by a staff nurse using the Timed Up and Go test and the Tinetti Performance-Oriented Mobility Assessment Tool.

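### The fall-risk score analysis is mis-stated: an unpaired test is placed within a group, no between-arm contrast of the score is named, and the Poisson model leaves the scale and variance of TUG and POMA open

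*Protocol article*

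**What the plan says.** All of the following is in the protocol article.

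- **Efficacy measures.** The Abstract (Results) gives two: how often participants fall, and how their fall-risk scores change.
- **Measurement.** Baseline Assessment says "Once the baseline data collection is completed, they will be assessed for fall risk", using TUG and POMA. The Follow-Up Phase repeats the fall-risk assessment every 3 months for a year.
- **Tests of the score.** Data Analysis pairs repeated measures ANOVA (or Friedman) with the unpaired *t* test (or Mann-Whitney) and says they "will be used to assess the within-group fall risk score at different time points and at each time point within the group, respectively".
- **Test of the category.** "The chi-square test will be used to analyze the fall risk score category at each time point between the groups".
- **Regression.** Poisson models are planned for "the number of falls and fall risks assessed using Timed Up and Go and the Performance-Oriented Mobility Assessment", with "independent factors (eg, age, gender, education, chronic illness, and intervention category" as explanatory variables. "Adjusted risk ratios with 95% CIs will be reported for the factors included in the multivariate Poisson regression model".
- **Two terms.** Fall risk is treated as categorical in one sentence ("The occurrence of falls and fall risk during the study period will be summarized as frequency and percentages"). The fall-risk score is treated as continuous in another, by mean and SD or median and IQR.
- **Randomization.** Treating physicians are randomized, stratified by seniority, and participants are treated by a physician of their group.

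**The concern.** An unpaired *t* or Mann-Whitney test compares two independent samples. Within one group at one time point there is only one sample, so the test as written cannot be done. The other pair of tests follows the score over time, but inside each arm. A statistician who follows the text literally therefore has no between-arm test of the score or of its change, although that change is an efficacy measure.

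Improvement within an arm may reflect natural course, practice with a repeated performance test, or regression to the mean. In an open-label trial it cannot be credited to deprescribing without a comparison of the arms.

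The Poisson sentence adds a second difficulty. TUG is a time and POMA a performance score, and neither is a count. If they enter as scores, model-based Poisson standard errors assume that the variance equals the mean, which nothing guarantees. If they enter as at-risk categories, the model can give a risk ratio, but its standard errors are too large unless a robust variance is used. The text settles neither the scale nor the variance.

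**Working it through.** **1. Which between-arm analyses of fall risk are stated?**

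| Quantity | Method in Data Analysis | Compares arms? |
|---|---|---|
| Score over time | Repeated measures ANOVA or Friedman | No, within group |
| Score at each visit | Unpaired *t* or Mann-Whitney | Not as written |
| Risk category at each visit | Chi-square | Yes, unadjusted |
| TUG and POMA fall risk, scale not stated | Poisson with arm term | Yes, adjusted, exploratory |

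No group-by-time or baseline-adjusted contrast of the score is named.

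**2. Calibration of a plain Poisson model.** The article gives no figure for this point. I take 239 per arm from Sample Size; a two-sided, continuity-corrected calculation for 73% against 58.4% at 90% power gives 234, within 3% of it. The article gives no mean or SD for TUG or POMA, so those below are assumptions.

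For two arms of size n with mean m and standard deviation SD, the log ratio of means has

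- model-based SE = √(2/(n·m)); for m = 13 and n = 239, √(2/3107) = 0.0254;
- actual SE ≈ (SD/m)·√(2/n).

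Their ratio, actual over model-based, is k = SD/√m. The type I error of a nominal 5% test is then about 2·[1 − Φ(1.96/k)]. For a binary outcome with risk p, k = √(1 − p). A null simulation (2,000 runs, individually independent participants, no covariates) agrees with the formula:

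| Assumed outcome | k | Formula | Simulated, model-based SE |
|---|---|---|---|
| TUG mean 13 s, SD 2 | 0.555 | 0.04% | 0.1% |
| TUG mean 13 s, SD 3 | 0.832 | 1.9% | 2.1% |
| TUG mean 13 s, SD 4 | 1.109 | 7.7% | 7.6% |
| TUG mean 13 s, SD 6 | 1.664 | 23.9% | 22.6% |
| Binary, p = 0.3 | 0.837 | 1.9% | 1.8% |
| Binary, p = 0.5 | 0.707 | 0.6% | 0.6% |
| Binary, p = 0.7 | 0.548 | 0.03% | 0.0% |

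For POMA (assumed mean 22, values rounded and cut off at 28 in the simulation), the simulated error was 0.2%, 1.4% and 7.7% for SD 3, 4 and 6 before the cut-off. With robust standard errors every scenario, score or binary, gave 4.4% to 5.4%.

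**3. Unit of TUG, if it enters as a score.** Recording in tenths of a second multiplies both m and SD by 10. Then k = 10·SD/√(10·m) = √10·SD/√m, so k and the model-based z statistic grow by √10 = 3.16 with no change in the data.

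**4. Value of baseline adjustment.** Against an unadjusted comparison of follow-up values, adjusting for baseline leaves a share 1 − r² of the residual variance, where r is the baseline-to-follow-up correlation. The r values are assumed.

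| r | 1 − r² | Reduction |
|---|---|---|
| 0.5 | 0.75 | 25% |
| 0.6 | 0.64 | 36% |
| 0.7 | 0.51 | 49% |

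**The case against.** **The within-group wording is a slip.** The preceding sentence on falls pairs tests between and within groups, so the unpaired test was almost certainly meant to compare the arms. This largely stands. Once corrected, there is a between-arm comparison of the score at every visit, and under randomization a comparison of follow-up values estimates the arm effect without a change score. What remains is that the printed text is wrong, and that even when corrected it offers a series of separate unadjusted visit tests rather than one longitudinal contrast.

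**A between-arm effect is planned.** A reader might infer that the plan yields no valid adjusted between-group effect at all. The document does not support that. The Poisson model contains the intervention category and reports adjusted risk ratios with confidence intervals, and the chi-square test compares the arms. For dichotomized fall risk with a suitable robust variance, that risk ratio would be valid.

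**Fall risks may mean categories.** The Poisson sentence speaks of fall risks, not scores, and promises risk ratios, which fits an at-risk category. This is a fair reading and the text does not exclude it. The unit argument therefore applies only if TUG enters as a score, and removing Poisson altogether is not justified. The category reading still leaves model-based errors conservative.

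**Baseline adjustment and robust variance may sit elsewhere.** The covariate list is given as examples, and a fuller plan may exist, so neither omission is itself an error. That stands, and the finding does not rest on either.

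**The trial is sized on falls.** That is true and limits the weight of the point, but the Abstract still presents change in the scores as efficacy.

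**Conclusion.** The point holds as a mis-stated analysis of an efficacy measure. The unpaired test is assigned where it cannot apply, the tests over time are within-arm only, and no between-arm contrast of the score or its change is named beyond an unadjusted chi-square test of the category and an exploratory Poisson model of unstated scale.

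If that Poisson model is fitted with model-based errors, it is miscalibrated on either reading. For scores, the simulated type I error ran from 0.1% to 22.6% for TUG and 0.2% to 7.7% for POMA; for categories it ran from 0.0% to 1.8%. These figures rest on the assumed means, SDs and risks. The simulation had no clustering by physician, so the 4.4% to 5.4% under robust errors shows only that the variance choice matters. It does not show that an unclustered robust error would be sufficient here.

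The 25% to 49% cut in residual variance is a gain in precision under an assumed correlation of 0.5 to 0.7, not evidence that the plan is invalid.

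**What to change.** 1. Correct the sentence in Data Analysis so that the unpaired *t* (or Mann-Whitney) test compares the two groups at each time point, and label it descriptive.
2. For TUG and POMA separately, make the main score analysis a linear mixed model on all 3-monthly values. Fixed effects: baseline score, visit, arm, arm-by-visit and seniority stratum. Random effects: participant and physician, since Randomization allocates physicians. Report the arm difference at 12 months with its 95% CI. Fix the scale of TUG (raw or log) in advance.
3. Keep Poisson regression for TUG and POMA only for dichotomized fall risk, state the cut-offs, and use a robust variance clustered by physician. The article gives no number of physicians; if there are few, specify a small-sample correction.

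The cost is wording and analysis time. TUG, POMA, visit, arm and seniority are already part of the trial; the treating physician must be recorded for each participant.

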### Randomization

#### Prescriber or Clinician randomization

After obtaining written informed consent, all treating physicians will be randomized using a stratified randomization method based on seniority in our study design. The clinicians will be divided into strata based on their seniority levels, for example, junior resident, senior residents, mid-level doctors (eg, assistant and associate professor levels), and senior doctors (eg, additional professor and professor cadre level). They will then randomly assign participants within each stratum to the intervention or control group. This stratified randomization ensures an equal distribution of doctors across the study groups, minimizing the potential for bias and contamination. Additionally, it accounts for any potential variations in expertise, experience, or treatment preferences among doctors of different seniority levels. The random allocation sequence will be generated using computer-generated random numbers. Enrolled participants will then be treated by the clinician randomized to the respective group.

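### The named between-arm falls test is unadjusted, and the exploratory Poisson model names neither baseline fall history nor the seniority stratum, so some precision is given up

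*Protocol article*

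**What the plan says.** All references are to the protocol article.

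- **Baseline Assessment.** Prior falls are recorded for every participant: "Participants will then be asked about their previous fall history using the fall history questionnaire".
- **Prescriber or Clinician randomization.** "all treating physicians will be randomized using a stratified randomization method based on seniority". The reason given is that expertise, experience and treatment preferences may differ by level. Enrolled patients are then treated by a clinician of the arm concerned.
- **Data Analysis, between-arm test.** Falls are compared between arms at each time point with a Mann-Whitney U test. No covariate or stratum is attached to it.
- **Data Analysis, adjusted model.** A Poisson regression, described as exploring associations, relates the number of falls to "independent factors (eg, age, gender, education, chronic illness, and intervention category". Covariate-adjusted risk ratios with confidence intervals will be reported from it.
- **Data Analysis, subgroups.** "Subgroup analysis will be performed for participants with recurrent fall history and different age categories". This is the only use of fall history that the section names.
- **Sample Size.** The trial is sized on the proportion who fall: "Considering the reported fall incidence with FRIDs as 73" per cent, with a "relative risk reduction of 20" per cent, 90% power and a 5% level.

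**The concern.** A patient's earlier falls are the baseline counterpart of the outcome on which the trial is sized. They are collected from everyone, and the plan treats them as relevant enough to define a subgroup. Seniority is the only stated stratification factor. Yet the one named between-arm falls test can use neither, and the adjusted model gives education as an example covariate while naming neither of these two.

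Two things are at stake, and they are two views of the same loss:

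- Variation between patients that prior falls could explain stays in the error term, so power is lower than the data allow.
- If the arms differ by chance in prior fallers, the unadjusted estimate moves with that difference. Balancing clinicians by seniority does not balance their patients' fall histories. Because patients follow their clinician's arm, such differences can be larger than under individual randomisation.

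The argument for seniority is different and smaller. Stratification already balances clinicians on it, so the point is only that the analysis should reflect the design. If seniority predicts falls, ignoring the strata makes the standard error somewhat too wide on that account alone.

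**Working it through.** **1. The plan's own figure.** Inputs from Sample Size: control proportion 0.73; intervention 0.73 × 0.8 = 0.584; difference 0.146; power 90%; level 5%, taken as two-sided because the sidedness is not stated.

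n per arm = [1.960 √(2 × 0.657 × 0.343) + 1.282 √(0.73 × 0.27 + 0.584 × 0.416)]² / 0.146² = (1.316 + 0.850)² / 0.0213, which rounds up to 221, or 234 with continuity correction. The article says "the sample size is estimated to be 478 (each arm: 239" per arm. The corrected figure is within 3%, so the calculation is reproduced.

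Power at 239 per arm, without the correction: Φ[(0.146 √239 − 1.316) / 0.663] = Φ(1.42) = 92.2%.

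**2. Power with adjustment, proportion of fallers.** The prognostic strength of fall history is not in the documents and is **assumed**: 30% to 50% of patients with prior falls, and a risk ratio for falling of 1.3 to 1.8. This corresponds to R² = h(1−h)(b−a)² / (0.73 × 0.27) of about 0.04 to 0.24. Here h is the share of prior fallers, and a and b are the risks without and with prior falls. Adjustment acts roughly like dividing n by (1 − R²):

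| R² | Power at 239 per arm | n per arm for 90% |
|---|---|---|
| 0 | 92.2% | 221 |
| 0.05 | 93.4% | 210 |
| 0.10 | 94.6% | 199 |
| 0.15 | 95.6% | 188 |
| 0.20 | 96.6% | 177 |

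Simulation as a check (239 per arm, individual randomisation, robust standard errors, 2,000 runs, 40% prior fallers):

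- History risk ratio 1.3: 91.1% becomes 92.2%.
- History risk ratio 1.5: 92.0% becomes 94.1%.
- Weaker treatment effect (risk ratio 0.85) with history risk ratio 1.5: 71.7% becomes 75.4%.

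The gain is about 1 to 4 points.

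**3. Fall counts.** Assumed: control mean 1.31 falls, dispersion 0.5, treatment rate ratio 0.8, 40% prior fallers; Poisson model with robust errors, 600 runs. Power goes from 52.5% to 54.0% when the history rate ratio is 1.5, from 47.2% to 51.0% when it is 2, and from 46.2% to 53.0% when it is 3. The gain is about 2 to 7 points. With so few runs the levels are rough; both models were fitted to the same simulated data.

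**4. Chance imbalance.** The SD of the arm difference in prior fallers is √(2h(1−h)/239). At h = 0.4 this is 4.5 points, with a 95% limit of 1.96 × 4.48 = 8.8 points. For h from 0.3 to 0.5 the limit is 8.2 to 9.0 points. The shift in the risk difference is the imbalance times (b − a). At h = 0.4 and risk ratio 1.5:

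- a = 0.73 / (0.6 + 0.4 × 1.5) = 0.608 and b = 0.9125
- shift = 0.088 × 0.304 = 2.7 points

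Across the feasible combinations the shift is 1.7 to 3.9 points, or about 11% to 27% of the 14.6-point target. For scale, the unadjusted 95% half-width is 1.96 √[(0.1971 + 0.2429)/239] = 8.4 points, so this shift already lies inside the stated uncertainty.

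**5. Shared clinicians.** The documents give no clinician count or intracluster correlation. If the design effect were 1.5 (assumed), a patient-level analysis would understate the standard error by a factor of √1.5 = 1.22.

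**The case against.** **The covariate list is open, and an adjusted effect is already planned.** This stands in part. The list is illustrative, intervention category is in the model, and a fuller protocol or analysis plan may complete it. A reader might infer that fall history and seniority are excluded from every falls analysis. The text does not support that: it does not name them as covariates, and recurrent fall history does define a subgroup. But the Mann-Whitney test stays unadjusted whatever the list later contains, and the Poisson model is presented as exploratory.

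**The between-arm test is worded as a test of change, which might use a baseline value.** The article does not say change from what. Even a change from baseline would not be the same as adjusting for the baseline value.

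**The size is assumed.** This stands. A reader might infer a gain of 5 points or more for the proportion of fallers. That needs strong prediction: at 40% prior fallers and a risk ratio of 1.8, 99.5% of prior fallers would fall again, against 55% of the others. The figures also describe a comparison of two proportions or a Poisson model, not the Mann-Whitney test itself.

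**Chance imbalance is not bias.** This stands. Under randomisation it is imprecision, already counted in the unadjusted standard error, and it does not inflate the type I error. Steps 2 and 4 should not be added together.

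**The unadjusted standard error might be called too large.** That holds only for ignoring the strata. Physicians are randomised, and ignoring patients who share one pushes the other way, possibly by more.

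**Conclusion.** The point holds in limited form. The named between-arm falls test is unadjusted, and the exploratory Poisson model names neither the fall history collected at baseline nor the randomisation stratum. Under the assumed prognostic strengths, this gives up about 1 to 4 points of power for the proportion of fallers and 2 to 7 for counts. It also leaves the unadjusted risk difference open to a shift of about 2 to 4 points at the 95% limit of chance imbalance under individual randomisation. Physician randomisation could widen that limit by an amount the documents do not allow one to compute. No size can be put on the seniority part.

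A reader might infer that the trial is underpowered or its result biased on this account. Neither follows: 239 per arm is reproduced, and the issue is efficiency and robustness. The change is worth making because it is nearly free.

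**What to change.** In Data Analysis, state before unblinding that the main between-arm falls result (proportion of fallers and number of falls) comes from a prespecified regression with:

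- intervention arm
- baseline fall history, for example 0, 1, or 2 or more prior falls
- physician seniority stratum
- age and gender
- cluster-robust standard errors or a random effect for the randomised clinician

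The last item is essential. A patient-level regression that ignores shared clinicians would give over-precise results. Keep the unadjusted comparison as a supporting analysis.

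The cost is a sentence or two. No new visits or patients are needed. Seniority is not among the listed baseline items, but it is known from randomisation; it and a coded clinician identifier need to reach the analysis file. With three history categories and the four example seniority levels, the model gains 2 + 3 = 5 parameters. A simple rule is needed for missing fall history, such as a separate category.
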